# Longitudinal profiling of the gut microbiome in patients with psoriatic arthritis and ankylosing spondylitis: a multicentre, prospective, observational study

**DOI:** 10.1186/s41927-020-00155-2

**Published:** 2020-11-10

**Keywords:** Psoriatic arthritis, Microbiome, Ankylosing spondylitis, Metabolomics, Gut-join axis

## Abstract

**Background:**

Psoriasis is a chronic inflammatory disease of the skin affecting 2–3% of UK population. 30% of people affected by psoriasis will develop a distinct form of arthritis within 10 years of the skin condition onset. Although the pathogenesis of psoriatic arthritis is still unknown, there is a genetic predisposition triggered by environmental factors. Limited but convincing evidence link the gut microbiome to psoriatic arthritis. The Microbiome in Psoriatic ARThritis (Mi-PART) study propose is to characterise the microbiome-metabolic interface in patients affected by psoriatic arthritis to deepen our understanding of the pathogenesis of the disease.

**Methods:**

This is a multicentre, prospective, observational study. Psoriatic arthritis (*n* = 65) and ankylosing spondylitis (*n* = 30) patients will be recruited in addition to a control group of healthy volunteers (*n* = 30). Patients eligibility will be evaluated against the Criteria for Psoriatic Arthritis (CASPAR), the Bath Ankylosing Spondylitis Activity Index (BASDAI) and the healthy volunteers who fulfil study inclusion and exclusion criteria.

Information regarding their medical and medication history, demographics, diet and lifestyle will be collected. All the participants in the study will be asked to complete a 7-day food diary, to provide stool samples and to complete quality of life questionnaires. Routine clinical laboratory tests will be performed on blood and urine samples. Patients and healthy volunteers with gastrointestinal symptoms, previous history of cancer, gastrointestinal surgery in the previous 6 months or alcohol abuse will be excluded from the study.

**Discussion:**

The aim of this trial is to characterise the microbiome of psoriatic arthritis patients and to compare it with microbiome of healthy volunteers and of patient with ankylosing spondylitis in order to define if different rheumatologic conditions are associated with characteristic microbiome profiles. Investigating the role of the microbiome in the development of psoriatic arthritis could deepen our understanding of the pathogenesis of the disease and potentially open the way to new therapies.

## Background

Psoriasis is a chronic inflammatory skin disorder that affects 2–3% of UK population [1]. It is characterised by a recurring erythematous papular rash without scars [2]. Psoriasis is associated with several different co-morbidities like a characteristic form of inflammatory arthritis [3]. Clinically, psoriatic arthritis (PsA) is mostly identified by the coexistence of psoriasis and arthritis, however PsA can present different patterns: distal and asymmetric oligoarthritis, symmetric polyarthritis, arthritis mutilans and spondyloarthritis [4]. PsA can induce joints damage quickly with 27% of patients showing irreversible damage in the first year from onset [5].

The pathogenesis of the disease is poorly understood however there is evidence of a genetic component in PsA, it has been demonstrated by studies showing an increased recurrence in first degree relatives [6]. Genes that have been demonstrated associated with an increased risk of developing psoriatic arthritis include HLA-B27, IL 13 and PTPN22, with the strongest association demonstrated for HLA B27 [7]. HLA-B27 is a well-established major risk factor for the development of ankylosing spondylitis (AS), but also 15–20% of PsA patients express HLA-B27 with a stronger association with the axial distribution of the disease [8, 9]. Additional risk factors for psoriatic arthritis include obesity [10], smoking [11], the presence of nail psoriasis and possibly the severity and distribution of psoriasis, some of these factors are linked to the host’s microbiome [12, 13].

In conclusion, several studies have demonstrated the presence of a network at the microbiota-metabolite-immunology level in the human setting of PsA, a chronic inflammatory disease [14, 15].

## Rationale

A growing number of evidence links alteration of the gut microbiome to the development of autoimmunity [16–18]. Studies conducted on animal models of ankylosing spondylitis using HLA-B27 rats have demonstrated the role of microbiome in inducing the disease [19, 20]. Scher et al. have recently identified a different gut microbiota in PsA patients and a concomitant reduction in short chain fatty acids (SCFA) when compared with healthy controls [21]. All these evidences suggest a link between an altered gut microbiome and PsA [12, 22]. Furthermore, there are several recognisable clinical patterns of PsA that overlap with AS and some cases may be even indistinguishable [4]. The study of the gut microbiome of PsA and AS patients brings an opportunity to compare if there is further differences that allow a more precise diagnosis of both diseases.

Thus, PsA is ideally suited to a phenomic approach of studying the mechanisms by which microorganisms and their metabolites affect immunity – investigating the gut and skin microbiome in the setting of inflammatory arthritis. This project should result in potential biomarkers of disease and putative signalling molecules for pharmacological analysis in the future. Additionally, by undertaking a metabolomic approach to the microbiome, novel therapeutic targets could be identified, and treatment approaches stratified according to the individual patients’ genetic and microbiomic drivers of inflammation.

## Study Aims

To stratify PsA and AS patients according to the disease activity and subtypes based on microbial networks.To deepen our understanding of psoriatic arthritis and to identify a panel of biomarkers that would allow stratification of patients according to the disease severity and therapy.Phenomic characterisation to determine how the microbiome interact with the host and potentially drive disease.To test the genetic predisposition to the development of the disease in association with environmental trigger factors.Use phenomic data to develop dietary or pharmaceutical interventions.

## Methods and analysis

### Study design

This is a multicentre, prospective and observational study to collect data and samples from consented males and females of any ethnicity origin aged over 18 years, diagnosed with psoriatic arthritis or ankylosing spondylitis or healthy volunteers from two geographical locations.
Royal National Hospital For Rheumatic Diseases (RNHRD), Bath, UK.Hammersmith Hospital, London, UK.

We will recruit a total of 125 subjects (95 PsA, 30 AS) and 30 healthy volunteers (Table 1). This study adheres to the principles outlined in the NHS Research Governance Framework for Health and Social Care (2nd edition) [23]. It is also conducted in compliance with the Data Protection Act and the Standard Protocol Items: Recommendation for Interventional Trials (SPIRIT) guidelines for clinical studies (Table 2).

**Table 1 Tab1:** The study is being recruited into four cohorts. The different number of visits is separated by 12 weeks

Group	Health Status	Number of subjects	Number of visits per subject
Group A	Psoriatic Arthritis	15	Screening, visit 1,2 and 3
Group B	Psoriatic Arthritis	50	Screening and visit 1
Group C	Ankylosing Spondylitis	30	Screening and visit 1
Group D	Healthy volunteers	30	Screening and visit 1

**Table 2 Tab2:** Standard Protocol Items: Recommendation for Interventional Trials (SPIRIT)

	Mi-PART STUDY PERIOD					
	Enrolment	Allocation	Post-allocation			Close-out
**TIMEPOINT(weeks)**	***-2***	**-1**	***0***	***12***	***24***	***T***_***24+***_ ***12 months***

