#### Sample size consideration

Estimate adequate sample sizes is complicated due to the lack of consensus in microbiome studies. Classical power calculations, used for clinical trials, are not a robust manner to assess the numbers of individuals required for exploratory and observational microbiome studies [34] since the SD and means of the sample populations is not known.

The recruitment strategy will be based on previous studies in inflammatory arthropaties [15, 21]. The variance in Th17, Treg numbers, IL-17 and IL − 22 cytokine measurements was estimated on the basis of previous clinical trials results [24]. Assuming a 2-sided significance level of 5% (a = 0.05) and a power 1-b of 95% (level at which we set the null hypothesis) and a 25% difference in IL − 17A secretion between controls and PsA, we needed to recruit a minimum of 24 study participants into each group (healthy volunteer, PsA and AS). Due to the nature of the sampling and the multiple visits to the clinic, we have set the target in 30 volunteers or more per group, to allow for dropout rate of 10% and to ensure robustness. First approach to subject lost to follow-up would be replaced to maximise data outcome and study objectives, otherwise the subject would be included with the acquired data.

In conclusion the study target to enrol 65 eligible patients with psoriatic arthritis (45 at the Bath centre and 20 at the London centre), 30 with ankylosing spondylitis, and 30 healthy volunteers.

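### The Study design sentence gives 95 PsA patients and implies 155 people; Table 1, the abstract and the sample size section give 65 PsA and 125 people in all

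*Protocol article*

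**What the plan says.** The protocol article gives the enrolment numbers in four places.

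- **Study design, text:** "We will recruit a total of 125 subjects (95 PsA, 30 AS) and 30 healthy volunteers (Table 1".
- **Study design, Table 1:** four cohorts. Group A is "Psoriatic Arthritis 15 Screening, visit 1,2 and 3", Group B is "Psoriatic Arthritis 50 Screening and visit 1", Group C is "Ankylosing Spondylitis 30 Screening and visit 1" and Group D is "Healthy volunteers 30 Screening and visit 1".
- **Abstract, Methods:** "Psoriatic arthritis (*n* = 65) and ankylosing spondylitis (*n* = 30) patients will be recruited", with 30 healthy volunteers as controls in addition.
- **Sample size consideration, closing paragraph:** "the study target to enrol 65 eligible patients with psoriatic arthritis (45 at the Bath centre and 20 at the London centre"), followed by 30 AS patients and 30 healthy volunteers.

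**The concern.** The Study design sentence points to Table 1 for its numbers and then disagrees with it. It attaches 95 to PsA, where the table has 65. It also sets the healthy volunteers beside a total of 125, although the table reaches 125 only by including them.

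PsA is the index disease, and its cohort size is a basic design fact against which recruitment and later reports will be judged. A reader who relied on the Study design text alone would expect 95 PsA patients. A fully recruited cohort of 65 would then look 30 short, or 30/95 = 32% below target.

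**Working it through.** **Inputs.** All are from the protocol article; no assumption is needed.

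| Source | PsA | AS | Healthy | All |
|---|---|---|---|---|
| Study design, sentence | 95 | 30 | 30 | 155 (by addition) |
| Study design, Table 1 | 15 + 50 = 65 | 30 | 30 | 125 |
| Abstract, Methods | 65 | 30 | 30 | 125 (by addition) |
| Sample size consideration | 45 + 20 = 65 | 30 | 30 | 125 (by addition) |

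**Step 1: the sentence on its own terms.** The bracket gives 95 + 30 = 125, which matches the total stated in front of it. The healthy volunteers are therefore outside that total: 125 + 30 = 155. The sentence does not print 155, but it follows from the wording. If 125 were meant to include the healthy volunteers, the bracket would have to add to 125 − 30 = 95. It adds to 125.

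**Step 2: the table that it cites.** PsA: 15 + 50 = 65. Patients: 65 + 30 = 95. All participants: 95 + 30 = 125. Table 1 thus yields both of the sentence's larger numbers with other meanings: 95 is the number of patients with either disease, and 125 is everyone.

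**Step 3: a further check on PsA.** The split by site, 45 at Bath and 20 at London, gives 45 + 20 = 65. This agrees with the split by cohort.

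**Step 4: size of the discrepancy.**

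- PsA: 95 − 65 = 30, and 30/65 = 46%.
- Implied total: 155 − 125 = 30, and 30/125 = 24%.
- The AS and healthy counts are the same in all four places, so the whole difference lies in the PsA count.

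**Step 5: does it reach the power statement?** The sample size section asks for at least 24 per group and allows for 10% dropout: 24/(1 − 0.10) = 26.7, rounded up to 27. The target is 30 or more per group. Both 65 and 95 exceed it, so the power statement stands or falls independently of this error.

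**The case against.** The best defence is that the article resolves the slip itself. Three statements agree on 65/30/30, one of them is the table that the sentence cites, and the site-level target leaves no doubt about what is intended. The number 125 is also correct as the total of all participants. All of this stands, and it is why the point is minor. It does not make the sentence right: the wording labels 95 as PsA and puts the healthy volunteers outside the 125, and no reading of it gives 65/30/30.

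A reader might go further in three ways that the article does not support.

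- **That repeat samples will be analysed as separate people.** The number 95 also equals the PsA study visits without screening (15 × 3 + 50 = 95), which could suggest that samples were counted as patients. But the sentence speaks of recruiting subjects, and the analysis section neither uses 95 as an n nor says that Group A's repeat samples will be pooled as independent. The Discussion presents the three-visit group as the means of studying change over time. The match also depends on leaving out screening, which Table 1 lists for every group. With screening, the PsA visits number 15 × 4 + 50 × 2 = 160.
- **That recruitment will run to the wrong number.** No rule for ending recruitment is tied to 95. The closing target in the sample size section is 65, given by site.
- **That the study's power is misjudged.** The power statement uses neither 95 nor 155.

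**Conclusion.** The Study design sentence misstates the sample size. It gives 95 PsA patients where every other statement in the article gives 65, an excess of 30 (46%), and it implies 155 people where the others give 125, an excess of 30 (24%). The conclusion rests on addition alone.

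The probable cause is that the number of patients, 65 + 30 = 95, was written as the PsA count. AS was then counted a second time, and the healthy volunteers were added to a total that already held them. That explanation is an inference; the contradiction does not depend on it.

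The error is one of statement. It shows no fault in the power calculation, the planned analysis or the recruitment targets by site. It is a minor correction, but a necessary one, because a sample size stated in the Methods should agree with the table it cites.

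**What to change.** Reword the one sentence in Study design so that it agrees with Table 1, for example: *The study will enrol 125 participants in total: 95 patients (65 with PsA and 30 with AS) and 30 healthy volunteers (Table 1).*

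This matches the abstract, Table 1 and the sample size section, none of which needs editing on this point. The cost is one sentence. The design, the targets and the power statement stay as they are.

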**ENROLMENT**						
**Eligibility screen**	X					
**Informed consent**	X					
**Clinical assessments**		X				
**Allocation**		X				
**ASSESSMENTS**						
***Baseline variables***	X	X	X	X	X	
***Outcome variables***			X	X	X	X
***Data process variables***				X	X	X

### Participants and recruitment

The patients will be recruited from rheumatology clinics under consultant’s advice. Self-referred patients will be involved through advertisements on noticeboards or websites/newspapers. All the questionnaires, indexes and scores mention in this section are detailed in the Additional file 1.

Any male or female patients older than 18 that fulfil the CASPAR or the BASDAI criteria will be invited for screening. They will receive the full patient information sheet (PIS) and informed consent forms (ICF). Potential participants will be allowed to consider full implications of taking part in the study for a minimum of 24 h before screening. They will also have the opportunity to ask questions before signing the consent.

Patients will not be able to take part to the study if they:
Are not able to give informed consentAre pregnant or breastfeedingHave a history of alcohol, drugs or chemical abuse in the 3 months prior to screeningHave recently changed their diet (less than 4 weeks)Have not been on a stable therapy with DMARDs in the 3 months prior to enrolmentExperienced any gastrointestinal symptom (diarrhoea, vomiting, abdominal pain, constipation) in the 4 weeks prior enrolmentTaken antibiotics in the 3 months prior to enrolmentHave been diagnosed with cancer in the past 3 years or any primary or secondary immunodeficiencyHave had endoscopy procedures carried out in the 8 weeks prior to enrolment or any gastro-intestinal surgery in the last 6 monthsMake regular use of laxatives and/or agents that affect gut motility

The healthy volunteers will be approached by the healthy volunteer data manager at Imperial College London and will also able to self-refer through advertisements. After consenting there will be a questionnaire. The volunteer will be asked to complete a self-description of health. This will be evaluated by one of the investigators, and any healthy volunteer with no current medical conditions and not in use of prescribed or self-prescribed medication (except for multivitamins) will be enrolled in the study.

All the participants to the study will receive a physical examination with assessment of vital signs (pulse and blood pressure), weight, height and body mass index (BMI). The medical and medication history will be reviewed with collection of data on demographics, diet and lifestyle. All concomitant medications will be recorded, including probiotics or fermented milk products.

Patients with AS will be evaluated with the Bath Ankylosing Spondylitis Disease Activity Index (BASDAI), the Bath Ankylosing Spondylitis Functional Index (BAFMI) and the Bath Ankylosing Spondylitis Metrology Index (BASMI). Patients with PsA will be evaluated following the CASPAR criteria, the Psoriasis Area and Severity Index (PASI) and the Composite Psoriatic Disease Activity Index (CPDAI). In cases where dactylitis or enthesitis are features, the Leeds Dactylitis Index (LDI) and the Leeds Enthesitis Index (LEI) will be included, respectively. BASDAI, BASMI and BAFMI will be used in cases of PsA with spondyloarthropathy.

All patients will have to complete a Health assessment questionnaire (HAQ), Visual Analogue Scoring (VAS) and a 7-day food diary. PsA patients will have also to complete a Dermatology Life Quality Index Questionnaire (DLQI).

Routine clinical laboratory tests will be performed on all patients other than healthy volunteers, including: full blood count (FBC), liver function tests (LFT), urea and electrolytes (U&E), C-reactive protein (CRP), erythrocyte sedimentation rate (ESR) (London site) / plasma viscosity (PV) (Bath site). Samples will be collected for analysis from all patients: serum, plasma, urine and faeces, as well as DNA assessment.

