### Withdrawal criteria

Study participants will be informed that they have the right to withdraw from the study at any time for any reason, without prejudice to their medical care. The investigator can withdraw subjects from the study for any of the following grounds:
Subject request.Subject is lost to follow-up (LTFU).Development of an intercurrent illness, condition, or procedural complication, which would interfere with the subject’s continued participation.The investigator also reserves the right to withdraw subjects in the interest of subject safety and welfare.

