## Discussion

Growing evidence during recent years has linked gut microbiome alterations with an increased disposition to develop chronic rheumatic diseases [15]. Particularly, the PsA link to the microbiome has been the target of a number of promising studies [12, 37–40]. However, there is a paucity of information at the microbiota-metabolite-immunology network level in the setting and development of the disease.

Taking into consideration the gap between these early stages of the research and clinical applications or therapeutic benefits. MI-PART is a multicentre, prospective, and observational study that aims to reduce the gap, undertaking a deep phenomic analysis.

Mi-PART study design acknowledges the heterogeneous manifestations of rheumatic diseases, particularly PsA. Previously, this has led to inaccuracies in the recruitment of patients for clinical studies [41]. All the recruitments in our study fulfil CASPAR Criteria [42] which has been proven the most feasible, specific and sensible for PsA diagnosis [43]. Mi-PART ensures a relevant number of recruitments since it has access to the Axial Disease in Psoriatic Arthritis (ADIPSA) [9] which counts with 200 PsA patients and also 200 AS patients that will set a cohort to analyse the heterogeneous manifestations of PsA and possible overlapping between the two diseases.

Previous studies have reported the relevance of control populations that should be used for microbiome studies [44, 45]. This study will recruit, in the first place, relatives of the PsA patients recruited for the study in order to ensure a similar background. In any circumstance, healthy controls sex, age, ethnicity, etc. will match the features of the PsA cohort to minimise environmental variables, particularly sensible in microbiome studies. Diet of all the participants in the study will be assessed using a 24-h food recall questionnaire for the previous 7 days of every visit during the study.

Diet pivotal role [31, 46, 47] in this study accounts for its connection with gut microbiome dynamics and high plasticity. However, an even bigger challenge is to understand and reconstruct the gut microbiome variability across time, for that reason longitudinal studies are extremely important. To address this, a PsA group in the study will have three different time points with a 12-week separation.

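### The antibiotic, diet-change and endoscopy exclusions are written for patients only, so healthy controls can enter with recent exposures that bar a patient; on four other exclusions the Abstract and the Methods disagree

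*Protocol article*

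**What the plan says.** The Protocol article, section Participants and recruitment, contains two entry rules.

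- **Patients.** The exclusion list opens "Patients will not be able to take part to the study if they". It includes having taken "antibiotics in the 3 months prior to" enrolment, a diet change less than 4 weeks old, gastrointestinal symptoms in the 4 weeks before enrolment, and endoscopy in the 8 weeks before enrolment. It also covers gastrointestinal surgery in the last 6 months, cancer in the past 3 years, and alcohol or drug abuse in the 3 months before screening.
- **Healthy volunteers.** A later paragraph, based on a self-description of health, says that "any healthy volunteer with no current medical conditions and not in use of prescribed or self-prescribed medication (except for multivitamins) will be enrolled". It has no look-back period and does not refer to the list above.

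The Abstract (Methods) differs: "Patients and healthy volunteers with gastrointestinal symptoms, previous history of cancer, gastrointestinal surgery in the previous 6 months or alcohol abuse will be excluded". It also speaks in general terms of "the healthy volunteers who fulfil study inclusion and exclusion criteria".

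On follow-up, the Discussion says that "a PsA group in the study will have three different time points with a 12-week separation". Table 1 identifies this as Group A, with 15 patients; every other group has screening and visit 1 only. Among the grounds on which the investigator can withdraw a subject, Withdrawal criteria lists "Development of an intercurrent illness, condition, or procedural complication, which would interfere with the subject’s continued participation". It names neither antibiotics, diet change nor endoscopy.

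**The concern.** The study hypothesis (Trial challenge) is that the microbiome-metabolic interface in PsA is distinct from that of healthy volunteers. By excluding patients with recent antibiotics, diet change or endoscopy, the protocol treats these as disturbances that make a stool sample unsuitable. Trial challenge itself cites evidence that a diet change can alter the microbiome within a day or two. If the rule binds one side of the comparison only, part of any observed difference, or lack of one, may reflect who was allowed in rather than disease.

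The direction is not fixed. Suppose recent antibiotics lower diversity, and suppose PsA patients are less diverse, as in the earlier 16-patient study described in Trial challenge. Exposed controls would then shrink the contrast. Recent diet changes could move it either way. The conclusion of the Discussion claims a design that minimises possible confounders, and a one-sided entry rule works against that claim.

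**Working it through.** The protocol gives no figure on this point, so the check is a comparison of texts.

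**Step 1. Who is bound by each exclusion**

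| Item | Methods list (patients) | Methods rule for volunteers | Abstract (both groups) |
|---|---|---|---|
| Antibiotics | 3 months before enrolment | current medication only | not named |
| Diet change | under 4 weeks, no anchor date | not named | not named |
| Endoscopy | 8 weeks before enrolment | not named | not named |
| Gastrointestinal symptoms | 4 weeks before enrolment | only if a current condition | named, no window |
| Gastrointestinal surgery | 6 months | not named | named, 6 months |
| Cancer | 3 years | only if a current condition | named, no window |
| Alcohol abuse | 3 months before screening | not named | named, no window |
| Regular laxatives or motility agents | yes | largely caught by the no-medication rule | not named |

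The first three rows bind patients and nobody else, wherever one looks. The next four are a conflict between two sections: the Abstract extends them to volunteers, the Methods do not.

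**Step 2. Is the list really addressed to patients?** It follows a paragraph on patients who meet the disease criteria and contains an item on stable therapy with disease-modifying drugs, which can apply to patients only. Volunteers are then introduced separately with their own positive rule. The layout supports the literal reading.

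**Step 3. Size for the control comparison.** If a share f of controls carries an exposure that shifts the outcome by s standard deviations, the control mean moves by f × s. The document gives neither f nor s, so no value follows from it.

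**Step 4. Follow-up (Group A only).** From Table 1, and assuming one sampling per numbered visit:

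- Follow-up samplings: 15 × 2 = 30.
- All planned samplings: 15 × 3 + 50 + 30 + 30 = 155.
- Share: 30 / 155 = 19%.

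Table 2 places the eligibility screen at week −2. Taking visit 2 as week 12, the gap is 14 weeks × 7 = 98 days, against about 91 days in 3 months. The whole antibiotic look-back before visit 2 therefore falls after the only check, and the same is true of visit 3. The 30 samplings are a ceiling on what the entry check does not cover, not an estimate of how many would be exposed.

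**The case against.** The best reply has five parts.

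- **The article may be a condensation.** The Abstract's reference to study criteria for volunteers suggests that such criteria exist. But the phrase points to no list containing antibiotics, diet change or endoscopy, and the Methods do not leave the matter open: they state a complete rule under which any qualifying volunteer is enrolled.
- **The article uses the word patients loosely.** The paragraph on routine laboratory tests speaks of all patients other than healthy volunteers, as if volunteers were a kind of patient. This lowers certainty about intent. It does not outweigh the separate volunteer paragraph and the item on disease-modifying drugs.
- **Exposures are recorded.** Medication history and concomitant medication are collected for all participants, and diet is assessed for the 7 days before every visit. This stands as partial mitigation, since it permits later adjustment. It is not an entry rule, and adjusting or discarding within a control group of 30 is a poor substitute for one.
- **Controls are relatives first, or otherwise matched.** Matching on background and demographic features does not address a recent course of antibiotics.
- **For follow-up, an observational cohort may legitimately keep real-life exposures.** Handling of such samples is commonly left to the analysis plan. This stands, and it limits the Group A point to collecting and flagging the information.

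Two stronger readings are tempting. A reader might infer that volunteers with gastrointestinal symptoms are plainly admitted; the Abstract excludes them, so that item is a contradiction and not a patients-only rule. A reader might also infer that an exposed Group A sample will be analysed as an ordinary observation; the article says nothing on this, and the inference rests on silence alone.

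**Conclusion.** The point holds for antibiotics, diet change and endoscopy: as written, controls may carry recent disturbances that disqualify patients, and this can bias the PsA-control comparison. For gastrointestinal symptoms, cancer, gastrointestinal surgery and alcohol abuse, the finding is that the Abstract and Participants and recruitment disagree and must be reconciled.

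The bias cannot be sized from the document. One could assume that 10 to 20% of the 30 controls (3 to 6 people) are exposed with a shift of 1 standard deviation. That moves the control mean by 0.1 to 0.2 standard deviations, which could then be expressed as a share of some assumed true difference. The exposed share, the shift and the true difference would all be assumptions without support in the text, so no percentage should be attached.

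The follow-up point is secondary. It concerns 15 patients and at most 30 of 155 samplings; Groups B, C and D have no follow-up visit. The statement that windows are tied to enrolment holds for antibiotics, gastrointestinal symptoms and endoscopy; the diet item has no stated anchor.

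**What to change.** 1. In Participants and recruitment, change the opening of the exclusion list so that the microbiome-relevant items, with the same look-back windows, apply to patients and healthy volunteers alike. Keep only the item on stable disease-modifying drugs patient-specific. State the date from which the diet-change window is counted.
2. Bring the Abstract into line with that list, so that gastrointestinal symptoms, cancer, gastrointestinal surgery and alcohol abuse read the same in both places.
3. For Group A, ask the antibiotic, gastrointestinal-symptom and endoscopy items again at each stool sample and flag any sample that falls inside a window. Leave the handling of flagged samples to the analysis plan.

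The cost is an eligibility wording change, a few volunteers screened out, and a short checklist at two further visits for 15 patients. The change is worth most before controls are sampled, because afterwards only exclusion or adjustment remains.
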